### vi) Specific scientific questions

1.  *Safety and immunogenicity of PCV under an accelerated 1-2-3 month schedule in PNG infants*

PCV has been shown to be safe and efficacious against IPD in SA infants given at 6-10-14 weeks of age ([name], pers comm). The standard PNG immunization schedule is at 1-2-3 months of age to achieve optimal vaccine coverage. PNG infants have higher Pnc carriage rates than reported in SA infants, which may affect immune responses to PCV. It is important that the reactogenicity and immunogenicity of PCV be established in this population at 1-2-3 months of age in comparison to control infants receiving the standard PNG infant immunizations. The response in SA infants after 1 and 2 doses of PCV at 6 and 10 weeks respectively suggests that fewer than 3 doses may be necessary in some populations (43). Therefore antibody responses to 1 and 2 doses will be examined. Immunogenicity will be primarily assessed by serotype-specific serum IgG at 2, 3 and 4 months of age, in comparison to responses in infants not receiving PCV.

2. *Safety and immunogenicity of neonatal immunization with PCV in PNG infants and comparison with early infant immunization*

Should infants be able to mount appropriate immune responses to PCV in the first week of life, then neonatal PCV should result in earlier protection against IPD due to vaccine serotypes and may provide protection against early carriage. Though neonatal responses to PCV may appear modest because of maternal antibody present, conjugate vaccines may still prime for memory (36). For our primary outcome, serum Pnc serotype-specific IgG antibody at age 2 months will be compared between neonatal PCV and control groups. This will assess whether there is a booster antibody response to the second dose of PCV in the neonatal group compared to infants given their first dose at 1 month of age and to naturally acquired antibody levels in the control group. This will determine whether neonatal PCV results in earlier protection, and monitoring will show whether safety has been compromised. We note that a safe and equally immunogenic outcome would be a more favourable response to neonatal PCV, since neonatal administration has the major logistic advantage of increasing uptake of the vaccine in the population.

*3. Induction of immunologic memory by neonatal and early infant PCV in PNG infants*

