Similar to concerns with early onset Pnc carriage, neonatal immunisation with PCV may result in preferential Th2 priming for the PCV carrier protein CRM197 which may affect subsequent responses to the virtually identical DT component of DTP vaccine. The potential for non-specific interference with responses to two additional “index” vaccines, the TT component of DTP vaccine which elicits a mixed Th0‑like response in infants which includes a strong Th2 component (64, 65), and the measles vaccine which elicits a response with a stronger Th1 component, will also be assessed. T‑cell cytokine responses to all these vaccines will be measured in the three study groups, to ascertain in particular whether neonatal PCV modulates the Th1/Th2 balance in host responses. Antibody responses to concomitant TT, Hib (PRP-TT) and DT will be measured at 4 months of age to ensure that there has been no interference with humoral immune responses. In this population all children achieve protective anti-tetanus and anti-diphtheria toxin antibodies after 3 doses of ActHib (76).

*(b)* *Non-specific interference with normal maturation of the immune system, in particular Th1 immunity*

Given the important role of microbial stimulation in driving the postnatal maturation of immune function(s), it is theoretically possible that PCV, particularly if given in the neonatal period, may contribute to this drive and hence accelerate the normal maturation process. This represents a possible safety issue, as (for example) precocious postnatal maturation of Th1 function may pose potential risks for inflammatory disease. Alternatively, PCV may promote non-specific Th2 immunity and delay Th1 maturation resulting in increased susceptibility to infectious and allergic diseases. Accordingly, specific analyses will be performed to contrast the kinetics of postnatal maturation of Th1/Th2 response capacity in groups with and without neonatal PCV.

*9. The impact of PCV on respiratory morbidity in PNG infants in the first year of life*

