**vii) Sample size requirements**

**Urban Rural n**

Group #2 #3 #1 #2 #3 #1 312

Block 1 13 13 13 13 52

Block 2 13 13 26 13 13 26 104

Blocks 3-4 26 26 26 26 26 26 156

The block randomisation schema is set out above. The sample size requirements were based on the primary questions and assumed 80% power and a 5% significance level. Distributions of published Pnc vaccine responses (21, 43, 44) indicate a standard deviation of serotype-specific IgG concentration of around 1 on the natural logarithmic scale, at all ages. For serious adverse reactions in Block 1, 26 subjects will be allocated to the post-neonatal PCV group 2 and 26 to the control group 3. This comparison will allow proportions of adverse events of e.g. 10% in the control group versus 48% in the treated group, or 5% vs 40%. If no serious adverse events occur in the first 26 treated children, it is likely that the true adverse event rate is 10% or less (and similarly in Block 2 for neonatal PCV group 1). Given 70% seroprotection (>0.5g/ml) after 1 dose of PCV at age 6 weeks (43), the sample size of 100 per group (min. 90 evaluable) allows this proportion to be estimated with 95% CI of 60-79% and will have 80% power at the 5% significance level to detect a 20% difference from group 1 (i.e. 90%) or group 3 (i.e. 50%).

For ALRI hospital admissions, assuming a rate of 0.0425 per child month under 1 year, a 50% decrease in either vaccinated group compared with controls is detectable. We can detect differences in carriage rates between the groups from 1 month onwards of say 40% down to 22% or lower.

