# **viii) Data analysis**

The principal analyses of efficacy and safety will be based on t-tests and chi-square tests. Further analyses examining the association of different factors such as number in household, housing type, town/country etc with response will use multiple regression methods: linear when IgG or cytokine level is the response, logistic when IgA, carriage or cytokine detection is the response, Cox when time to hospital admission or onset of carriage is the response, or Poisson when admission rate is the response.

Comparison of cytokine levels between the different groups at different times will employ the same basic methods; however, further analyses of immune competence will be slightly more complex in that the profile of within-person changes over time in antibody and cytokine levels will form the major response and explanatory variables. Thus 2-level models allowing for different levels of variability within and between children will be used, comparing in particular both level and rate of change of these measures. These regression models will also include terms for vaccination status as well as the other confounders such as crowding, sex etc.

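### Equal immunogenicity of the neonatal schedule and absence of interference with TT, DT and Hib are non-inferiority claims, but the protocol pairs them with difference tests, difference-only sizing and no margin

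*Protocol*

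**What the plan says.** Aim 2 asks whether neonatal PCV gives a better antibody response than starting at 1 month, without loss of safety. Section vi, question 2, names the primary outcome: "serum Pnc serotype-specific IgG antibody at age 2 months will be compared between neonatal PCV and control groups". It then adds a second way for the neonatal schedule to count as favourable, because giving vaccine at birth should raise uptake: "We note that a safe and equally immunogenic outcome would be a more favourable response to neonatal PCV".

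Section vi, question 8(a), covers concomitant vaccines. Antibody to TT, Hib and DT is measured at 4 months "to ensure that there has been no interference with humoral immune responses". It also reports, from an earlier study: "In this population all children achieve protective anti-tetanus and anti-diphtheria toxin antibodies".

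Section viii states: "The principal analyses of efficacy and safety will be based on t-tests and chi-square tests". Regression and two-level models follow as further analyses. Section vii says that the sizing "assumed 80% power and a 5% significance level". Its targets are all differences: 70% seroprotection against 90% or 50%, a halving of ALRI admissions, and carriage falling from 40% to 22%. The protocol states no equivalence or non-inferiority margin, and no confidence-interval rule for either conclusion.

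**The concern.** To say that one schedule is as immunogenic as another, or that a vaccine does not interfere, is to claim that any deficit is smaller than some tolerable size. A t-test or chi-square test of no difference does not address that. Failing to reject shows only that the data were not precise enough to exclude zero. Noise and missing samples then push the result towards the conclusion sought.

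The protocol itself gives reasons to take interference seriously. Its background describes carrier-specific suppression and reports a reduced response to later doses after one neonatal Hib conjugate. Question 8(a) notes how close CRM197 is to the diphtheria toxoid in DTP. An unsupported statement of no interference would therefore feed into the immunological safety case for neonatal PCV.

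**Working it through.** **Inputs.** All come from section vii: SD about 1 on the natural-log scale for pneumococcal serotype-specific IgG; 100 per group with at least 90 evaluable; 5% significance; 80% power. Sidedness is not stated, so I take two-sided.

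**The plan's own figure.** For two proportions, power = Φ{[|p1 − p2| − 1.96·√(2·p̄(1 − p̄)/n)] / √[(p1(1 − p1) + p2(1 − p2))/n]}.
- 70% vs 50%, n = 90: (0.20 − 0.143)/0.0715 = 0.795, power 78.7%. At n = 100, 82.8%.
- 70% vs 90%, n = 90: power 92.5%.
- Exact 95% CI for 70% at n = 100: 60.0% to 78.8%, matching the stated 60-79%.

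The stated sizing reproduces. It is sizing to detect a 20-point difference.

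**What non-significance allows on the GMC scale.** SE of the difference in mean log IgG = √(2/90) = 0.149.
- Largest observed deficit that is still non-significant: exp(−1.96 × 0.149) = 0.747.
- Lower 95% limit at that point: exp(−3.92 × 0.149) = 0.557, a concentration 44% lower.
- True ratio 0.80: −ln(0.80)/0.149 = 1.497, so the test is non-significant in 68% of trials.
- True ratio 0.75: 1.930, non-significant in 51%.

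**The same on the seroprotection scale (n = 90, 70% in one arm).** A true 10-point deficit is non-significant in 71% of trials and a 15-point deficit in 45%.

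**Effect of losing samples (illustration only).** With 60 evaluable per group, SE = √(2/60) = 0.183. The borderline ratio falls to 0.70 and its lower limit to 0.49.

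**What a margin would need.** The protocol gives none, so these margins are assumptions. With a true ratio of 1 and a one-sided 2.5% test, power per serotype = Φ(−ln(margin)/SE − 1.96).
- Margin 0.5, n = 90: 4.650 − 1.96 = 2.690, power 99.6%.
- Margin 0.67, n = 90: 2.686 − 1.96 = 0.726, power about 77%.
- Seroprotection, 70% in both arms, n = 90: power 31%, 59% and 83% for margins of 10, 15 and 20 points.

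**Across serotypes.** If all seven PCV serotypes had to pass and were independent, power would be 0.9964^7 = 97.5% at a margin of 0.5, but 0.766^7 = 15.5% at 0.67.

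**Proportion protected for DT and TT.** If 90 of 90 controls were protected, 84 of 90 in a PCV arm gives Fisher's exact p of about 0.03. A loss of protection of that size would show. A fall in concentration that stays above the threshold would not.

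**The case against.** The strongest reply is that the protocol never says a non-significant test will be read as equality or as no interference. A reader might infer it, but the text does not state it. Section viii also provides for linear regression and two-level models, which yield estimates with intervals, and the SAP, which is not shown, may hold a margin. This stands as a limit on the charge. It does not remove the mismatch: the protocol names difference tests as principal, sizes only for differences, and gives no rule by which an interval would support either conclusion.

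Second, the sentence on equal immunogenicity is a remark that follows the primary outcome, and a t-test suits that outcome. A reader might infer that the primary analysis is unsound; it is not.

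Third, one might argue that a ceiling makes proportion protected useless for detecting DT and TT interference. The documents do not support that. No chi-square on proportion protected is specified for these antigens. Section v mentions protective levels only in offering boosters, and the statement that all children are protected describes an earlier study. As shown above, such a comparison could reveal real loss of protection.

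Fourth, equality with the 1-2-3 month schedule is not a stated gate to an efficacy trial. The expected-outcomes section makes progression depend on neonatal PCV being safe. The safety monitoring board also looks for tolerance or immune suppression, and T-cell responses are compared across groups, so immunological safety does not hang on one p-value.

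**Conclusion.** The concern holds for two secondary conclusions: equal immunogenicity of group 1 and group 2, and no interference with TT, DT and Hib antibody. The principal analyses named cannot establish either. At 90 per group, a non-significant result is compatible with a GMC up to 44% lower in the borderline case, and a true 20% deficit would be non-significant about two times in three. The comparison of neonatal PCV with control at 2 months is unaffected.

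The figures assume a two-sided 5% test and an SD of 1, which the protocol gives only for pneumococcal IgG. They cannot be carried over to TT, DT or Hib, whose SD is not stated. The 0.56 limit belongs to the borderline observed ratio and is not a typical result. This should be corrected, but it does not undermine the trial's main comparison.

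**What to change.** For these two conclusions, report the GMC ratio with a two-sided 95% CI. Claim equality or no interference only if the lower limit exceeds a prespecified margin that the sponsor justifies; 0.5 and 0.67 are examples.

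- **Group 1 vs group 2.** Name the contrast that defines equal. Same-age serum at 4 months is available in all groups. Comparing group 1 at 3 months with group 2 at 4 months equalises the interval after the third dose but not age, so carriage and waning maternal antibody could differ; if it is chosen, say so. State the rule across the seven serotypes, since it drives power at the stricter margin.
- **TT, DT and Hib.** Compare groups 1 and 2 with group 3 at 4 months, and state the SD assumed. Keep proportion protected for DT and TT as a supplement to the GMC ratio.
- **Scale.** Use GMC for the margin. A 10-point seroprotection margin at 70% is out of reach at this size.

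The cost is wording, a justified margin, a named contrast and a serotype rule, with no extra infants or bleeds. The downside is that a claim of equality may fail where a non-significant test would have been read as support.

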**vii) Sample size requirements**

**Urban Rural n**

Group #2 #3 #1 #2 #3 #1 312

Block 1 13 13 13 13 52

Block 2 13 13 26 13 13 26 104

Blocks 3-4 26 26 26 26 26 26 156

The block randomisation schema is set out above. The sample size requirements were based on the primary questions and assumed 80% power and a 5% significance level. Distributions of published Pnc vaccine responses (21, 43, 44) indicate a standard deviation of serotype-specific IgG concentration of around 1 on the natural logarithmic scale, at all ages. For serious adverse reactions in Block 1, 26 subjects will be allocated to the post-neonatal PCV group 2 and 26 to the control group 3. This comparison will allow proportions of adverse events of e.g. 10% in the control group versus 48% in the treated group, or 5% vs 40%. If no serious adverse events occur in the first 26 treated children, it is likely that the true adverse event rate is 10% or less (and similarly in Block 2 for neonatal PCV group 1). Given 70% seroprotection (>0.5g/ml) after 1 dose of PCV at age 6 weeks (43), the sample size of 100 per group (min. 90 evaluable) allows this proportion to be estimated with 95% CI of 60-79% and will have 80% power at the 5% significance level to detect a 20% difference from group 1 (i.e. 90%) or group 3 (i.e. 50%).

For ALRI hospital admissions, assuming a rate of 0.0425 per child month under 1 year, a 50% decrease in either vaccinated group compared with controls is detectable. We can detect differences in carriage rates between the groups from 1 month onwards of say 40% down to 22% or lower.

# **viii) Data analysis**

The principal analyses of efficacy and safety will be based on t-tests and chi-square tests. Further analyses examining the association of different factors such as number in household, housing type, town/country etc with response will use multiple regression methods: linear when IgG or cytokine level is the response, logistic when IgA, carriage or cytokine detection is the response, Cox when time to hospital admission or onset of carriage is the response, or Poisson when admission rate is the response.

Comparison of cytokine levels between the different groups at different times will employ the same basic methods; however, further analyses of immune competence will be slightly more complex in that the profile of within-person changes over time in antibody and cytokine levels will form the major response and explanatory variables. Thus 2-level models allowing for different levels of variability within and between children will be used, comparing in particular both level and rate of change of these measures. These regression models will also include terms for vaccination status as well as the other confounders such as crowding, sex etc.

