# Demographic surveillance and recruitment of study participants

After informing communities about the study, a house-to-house census will be undertaken in those villages previously under surveillance in Lowa CD. Surveillance by local reporters will identify pregnant women, ensure close monitoring for safety of neonatal immunization for 18 months post-vaccination and re-establish a population base for future studies including an efficacy trial of neonatal PCV if appropriate. If necessary, surveillance will be extended to neighbouring villages to include a total population of more than 3000 in order to identify 100 pregnant women annually. A nurse will also recruit women through antenatal clinics at Goroka Hospital to enrol an equal number of urban children. In view of the intensive monitoring schedule, no more than 2 urban and 2 rural mothers will be recruited weekly. Data on URT carriage rates in the urban population are not available; however, we might expect later onset of URT Pnc carriage in babies living in the less crowded, more hygienic urban living conditions. By enrolling equal numbers of participants from urban and rural areas we can investigate the effect of early onset of carriage on subsequent immune responses. Following enrolment at antenatal clinic, a home visit will be done to collect social and demographic data on the entire household (for comparison between urban and rural areas). This will help re-establish an urban population base for future trials. Weekly surveillance of all households in enlisted villages and of enlisted families in Goroka will continue for the entire study period for safety monitoring, identification of potential new participants, registration of deaths and migrations in and out of the area. Each person under demographic surveillance is assigned a unique identifying number used to link all data.

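### Allocation is balanced within urban and rural strata but the principal tests ignore residence, which makes them mildly conservative if residence predicts the outcome

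*Protocol*

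**What the plan says.** In the Protocol, section vii (Sample size requirements), the allocation table has separate urban and rural columns for each group, and the text below it says "The block randomisation schema is set out above". Its rows read "Block 1 13 13 13 13 52", "Block 2 13 13 26 13 13 26 104" and "Blocks 3-4 26 26 26 26 26 26 156". The section on inclusion criteria and recruitment points to this table for the block randomization.

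The section on demographic surveillance and recruitment says of residence that "we might expect later onset of URT Pnc carriage in babies living in the less crowded, more hygienic urban living conditions", and gives a purpose for the equal split: "By enrolling equal numbers of participants from urban and rural areas we can investigate the effect of early onset of carriage on subsequent immune responses". It also says that there are no data on urban carriage rates.

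Section viii (Data analysis) sets the principal tests: "The principal analyses of efficacy and safety will be based on t-tests and chi-square tests". Residence appears in the next sentence: "Further analyses examining the association of different factors such as number in household, housing type, town/country etc with response will use multiple regression methods".

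**The concern.** When numbers per group are fixed within strata, the difference between strata cannot contribute to chance variation in the group comparison. An unstratified test still counts that difference as noise. If town and village infants differ in carriage, the reported intervals are wider than the design warrants, the test rejects less often than 5% under the null, and some precision already paid for in the allocation goes unused. The sentence on principal analyses covers safety as well as efficacy. For safety, a conservative test leans towards missing a difference, though again only if residence predicts the event.

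**Working it through.** **Inputs.** From section vii: 5% significance (taken as two-sided), 80% power, carriage 40% v 22%, 100 infants per group with at least 90 evaluable, and an SD of about 1 for ln IgG. The urban carriage rate is not given, so the stratum rates below are assumptions centred on the plan's 40%. For scale, Background section ii reports 41% v 12% colonised by 2 months in Aboriginal v non-Aboriginal children (a 29-point gap) and 60% acquisition in the neonatal period in the Asaro Valley.

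**1. Balance by residence.** In each of the urban and rural columns, groups 2 and 3 have 13 + 13 + 26 = 52 infants, and group 1 has 0 + 26 + 26 = 52. Each group therefore has 104 infants, half urban and half rural, and 3 × 104 = 312.

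**2. The plan's carriage figure.** For a pooled chi-square test without continuity correction, n per group = [1.96·√(2·0.31·0.69) + 0.842·√(0.4·0.6 + 0.22·0.78)]² / 0.18² = (1.282 + 0.540)² / 0.0324 ≈ 103. Power is 80.6% at 104, 79.0% at 100 and 74.7% at 90 per group. The stated figure reproduces at about full enrolment. The shortfall at 90 comes from the number of infants and not from the choice of test.

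**3. Why the pooled test is conservative.** With two equal strata whose rates differ by D, the pooled variance p(1−p) exceeds the mean within-stratum variance by D²/4. With no effect and p = 0.40, the ratio of true to nominal standard error is r = √[1 − (D²/4)/0.24], and the real type I error is 2[1 − Φ(1.96/r)]:
- D = 0.20: r = √(0.230/0.24) = 0.979, type I error 4.5%.
- D = 0.29: r = √(0.219/0.24) = 0.955, type I error 4.0%.
- D = 0.40: r = √(0.200/0.24) = 0.913, type I error 3.2%.

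**4. Power.** This was simulated with marginal rates held at 40% and 22%, a common odds ratio across strata and a 1:1 urban:rural split. Each power cell shows the pooled chi-square test, then the Mantel-Haenszel test.

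| Assumed control carriage, urban/rural | Power, 90 per group | Power, 100 per group | Type I error, pooled, 100 per group |
|---|---|---|---|
| 40/40% | 74.8 → 74.9% | 79.7 → 79.4% | 5.1% |
| 30/50% | 75.2 → 76.3% | 80.0 → 80.7% | 4.6% |
| 25.5/54.5% | 75.6 → 78.2% | 80.5 → 82.2% | 4.2% |
| 20/60% | 76.4 → 80.8% | 81.4 → 85.0% | 3.2% |

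The gains are 1.1 and 0.7 points (20-point gap), 2.6 and 1.7 points (29-point gap), and 4.4 and 3.6 points (40-point gap). In the 20/60% case the unstratified standard error is about 9% too large.

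**5. IgG.** With total SD 1 and 90 per group, the difference detectable at 80% power is (1.96 + 0.84)·√(2/90) = 0.418 ln units. If urban and rural means differ by d, the residual SD is √(1 − d²/4). Power, unadjusted then adjusted, is 80.1 → 80.4% for d = 0.2, 80.8 → 82.5% for d = 0.5 and 82.1 → 86.4% for d = 0.8. The protocol supports no particular d.

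**The case against.** The case for leaving the plan alone is substantial.

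- **Nothing promised is lost.** The pooled test's power rises slightly with the gap and never falls below the plan's own calculation. This stands. A reader might infer that the principal tests are invalid, biased or underpowered because of this choice. They are not: the loss is only relative to a stratified test.
- **The gap is undocumented.** Later onset in town is offered only as a possibility. The 29-point contrast comes from Western Australia, while the study villages adjoin Goroka, where living standards are said to vary widely. This stands. A reader might take a very wide gap, and so a large gain, as expected, but no figure in the protocol supports that.
- **Timing.** The expectation concerns onset. Carriage is sized from 1 month onwards, and Background section ii says that all Asaro Valley children acquire pneumococcus by 3 months. This stands, and it limits the point mainly to the early swabs.
- **The primary outcome.** Under question 2 of section vi this is serotype-specific IgG at 2 months. The protocol nowhere says that residence predicts IgG. Whether early carriage affects immune responses is a question for study. This stands.
- **Adjusted regressions are already planned, and covariates can be left to an SAP.** This stands only in part. An adjusted result would exist, but the protocol itself names the principal tests and puts town/country elsewhere. That is a choice made in this document, not a gap left open.

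One caution on remedies: adding the stratum to a logistic model can raise power but does not narrow the interval for the odds ratio.

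**Conclusion.** The point holds as a modest loss of efficiency. The allocation is balanced by residence, the protocol itself suggests that residence may matter for carriage, and the principal tests ignore it. If residence predicts the outcome, those tests are conservative. The realistic gain from stratifying the carriage comparison is about 1 to 4 points of power at 90 to 100 infants per group, and less than that if town and village differ little. These figures assume marginal rates of 40% and 22%, equal strata and a common odds ratio. The benefit is most plausible in the first weeks of life and is conditional for IgG. This is a free improvement and not the repair of a faulty test. It concerns residence only. Allocation also varies by block, which is a separate matter.

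**What to change.** In section viii, make the principal comparisons adjusted for the urban/rural stratum used in allocation:
- Carriage and seroprotection: a Mantel-Haenszel test with a stratum-adjusted risk difference and its interval.
- IgG and cytokine levels: linear regression of the log level on group plus stratum.
- Admission rate, time to admission and onset of carriage: the stratum as a fixed term in the Poisson and Cox models.

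Keep the unadjusted t-tests and chi-square tests as sensitivity analyses. Naming the adjusted result as principal in advance also avoids a later choice between two sets of results.

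The cost is wording and one degree of freedom. Residence is known at enrolment, so no further data, visits or infants are needed. If the strata do not differ, the loss is at most about half a point of power (79.7 → 79.4% in the 40/40% row at 100 per group).

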# Immunization schedule and follow-up

Village reporters will inform study staff if a woman has delivered outside hospital. A study nurse will visit the delivery ward at Goroka Hospital at least once daily to identify newborns to enrolled women. Following recruitment, infants will be randomized to one of three equal-sized groups to receive: 1) PCV at ages 0-1-2 months, 2) PCV at ages 1-2-3 months and 3) no PCV. Birthweight and weight at each follow-up visit will be recorded. Routine infant immunizations will be given in accordance with the PNG schedule (Table 1). As PCV has not been evaluated in this population previously, the first 52 infants will be randomized to groups 2 or 3 only, and the safety data will be reviewed by an independent safety monitoring committee. Conjugate Hib vaccine (ActHib), which is mixed with DPT, has recently been introduced into the immunization schedule in PNG, after being shown to be safe and immunogenic in this population when given at ages 1, 2 and 3 months (76). Since it is in short supply, we may have to purchase it. BCG and DPT/Hib are routinely administered in the deltoid muscle. Hepatitis B and measles will be given in the right thigh. PPV (at 9 months) and PCV will be given in the left thigh.

All immunizations will be given either in Goroka Hospital or at the PNGIMR clinic. Following immunization, children will be monitored at the clinic for 2 hours. Children will then be seen 1 and 2 days after each dose during primary immunization and on day 7 following PPV to check for local or systemic reactions. Children will be seen weekly by nursing staff to age 4 weeks. Guardians will be informed of time of appointments and transport to Goroka clinic will be arranged. If they fail to attend their appointment, we will make 3 further attempts to bring the children for routine follow-up. Guardians may choose to remove their child from the study at any time. Participants will cease to be in the study if they suffer an allergic reaction to vaccination or have inadvertently been given routine immunizations by someone other than the study nurses. All such children will continue to receive medical attention from clinic and field staff as required.

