**iii) Safety monitoring board**

A safety monitoring board (SMB) will be established, including independent clinicians from PNG and Australia. If the board finds nothing untoward following the first block of 52 immunizations of groups 2 and 3, the trial will then be authorized to proceed including neonatal immunization (group 1). Clinical and immunogenicity data will be sent regularly to the clinical monitors. Throughout the study, all adverse events will be reported and any serious adverse events will be immediately reported to the SMB. In particular, they will examine the data for any evidence of tolerance/immune suppression in addition to serious adverse events.

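### Contrasts with the neonatal group include controls enrolled before that group opens, and the principal tests carry no block term

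*Protocol*

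**What the plan says.** Under Immunization schedule and follow-up, "the first 52 infants will be randomized to groups 2 or 3 only". Section iii) Safety monitoring board makes the opening of group 1 depend on the board's review of that first block.

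The table in vii) Sample size requirements lists groups 2, 3 and 1 in that order, urban then rural. Its rows read "Block 1 13 13 13 13 52", "Block 2 13 13 26 13 13 26 104" and "Blocks 3-4 26 26 26 26 26 26 156". The text below it confirms that in Block 1 "26 subjects will be allocated to the post-neonatal PCV group 2 and 26 to the control group 3".

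On method, viii) Data analysis states: "The principal analyses of efficacy and safety will be based on t-tests and chi-square tests". Covariates appear only afterwards: "Further analyses examining the association of different factors such as number in household, housing type, town/country etc with response will use multiple regression methods". The two-level models add crowding and sex. Neither block nor enrolment period is named anywhere in the section.

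Item 2 of vi) Specific scientific questions makes the primary outcome serotype-specific IgG at 2 months, neonatal group against controls.

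**The concern.** The 26 control infants and 26 group 2 infants of Block 1 were never randomised against group 1. A plain t-test or chi-square test pools them with later infants as though all three groups had been open throughout. Any change in outcome level between Block 1 and Block 2 then enters the group 1 contrast as if it were a vaccine effect, in either direction. It could create an apparent benefit or hide a harm.

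Some change is plausible. At the recruitment cap of 2 urban and 2 rural mothers a week, Block 1 takes at least 52/4 = 13 weeks, and the safety review comes before group 1 opens. Block 1 is also the start-up phase, when the surveillance area is still being expanded. The trial is meant to show that neonatal vaccination is safe and does not interfere with other vaccines. Groups may differ little on those outcomes, so even a small bias counts.

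**Working it through.** **The plan's own totals.** Block 1: 4 x 13 = 52. Block 2: 4 x 13 + 2 x 26 = 104. Blocks 3-4: 6 x 26 = 156. Sum 312, or 104 per group, as stated.

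| | Block 1 | Block 2 | Blocks 3-4 |
|---|---|---|---|
| Group 1 | 0 | 52 | 52 |
| Group 2 | 26 | 26 | 52 |
| Group 3 | 26 | 26 | 52 |

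So 26/104 = 25% of groups 2 and 3 have no concurrent group 1 infants.

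**Bias of the pooled contrast with no vaccine effect.** Let B1, B2 and B34 be the mean outcomes in the three periods.
- Group 1 mean = 0.5 B2 + 0.5 B34.
- Control mean = 0.25 B1 + 0.25 B2 + 0.5 B34.
- Difference = 0.25 x (B2 - B1). Blocks 3-4 cancel.

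**Effect on the error rate.** The SD of ln IgG is 1 (section vii). With 104 per group, SE = sqrt(2/104) = 0.139. With d = bias/SE, the two-sided error is 1 - Φ(1.96 - d) + Φ(-1.96 - d). The protocol gives no drift, so the shifts are assumptions.

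| Assumed shift in ln IgG | Bias | d | Type I error |
|---|---|---|---|
| 0.1 | 0.025 | 0.18 | 5.4% |
| 0.25 | 0.0625 | 0.45 | 7.4% |
| 0.5 | 0.125 | 0.90 | about 15% |

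With 90 per group the last row is about 13%. For carriage, assume 40% from Block 2 onwards. Block 1 at 50% gives a spurious 2.5-point reduction and an error of about 7%; Block 1 at 60% gives 5 points and about 11%.

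**Dropping Block 1 without a block term is not enough.** Block 2 would hold 52/104 = 50% of group 1 but 26/78 = 33% of the remaining controls, leaving a bias of 0.17 x (B2 - B34).

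**Information after block stratification** (sum over blocks of n1 x n3/(n1 + n3)):
- Pooled: 104 x 104/208 = 52.
- Stratified: 0 + 52 x 26/78 + 52 x 52/104 = 17.3 + 26 = 43.3.
- Ratio 43.3/52 = 83%. This is equivalent to 86.7 per group at full numbers and 75 at the stated minimum of 90 evaluable.

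**Power, two-sided 5%** (sidedness assumed; normal approximation):

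| Contrast in section vii | Pooled, 104 / 90 | Stratified, 104 / 90 |
|---|---|---|
| 90% vs 70% | 96% / 93% | 92% / 87% |
| 40% vs 22% carriage | 81% / 75% | 73% / 67% |

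At full numbers the pooled carriage power of 81% agrees with the protocol's 80%. The difference in ln IgG detectable with 80% power and 90 evaluable rises from 0.42 to 0.46.

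**The case against.** The best defence is that t-tests and chi-square tests name a family of methods. Mantel-Haenszel is itself a chi-square test, and block terms are often left to an analysis plan, which is not shown here. This stands in part: the protocol does not forbid stratification. But it does name the principal tests, it places covariates only in further analyses, and the open-ended lists there do not commit to block. Adding a block term would change the stated principal method for the primary contrast.

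Several stronger readings are tempting and do not hold:
- A reader might infer that every group 1 comparison is in fact confounded with time. The documents establish the exposure, not a drift. Three quarters of the controls come from Block 2 onwards.
- A reader might infer that the 2:1:1 ratio in Block 2 adds a further bias. In the full pooled comparison it is catch-up, and only the Block 1 to Block 2 change matters.
- A reader might infer that leaving out urban/rural biases the contrast. Each group has 52 urban and 52 rural infants, so only precision is lost.
- A reader might infer a large distortion of ALRI admissions from enrolment season. The stated rate covers the first year of life, so a fully followed infant passes through all seasons. The protocol gives no basis for a large shift in the first-year rate.

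Two further mitigations are fair. Section v) Laboratory methods specifies a standardised ELISA, international control sera and blinded laboratory staff, which limits assay drift. And the planning values imply 90% in group 1 against 50% in controls, a 40-point difference that modest drift would not overturn.

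**Conclusion.** The point holds as a flaw in the stated principal method. The 25% non-concurrent share is certain from the block table, and so is the form of the bias, 0.25 x (Block 2 mean minus Block 1 mean). Its size is unknown because the protocol gives no drift figure. Across assumed ln IgG shifts of 0.1 to 0.5, the error rate runs from barely above nominal to about three times nominal, given SD 1 and 104 per group. The primary IgG contrast with controls is formally affected, but it is less vulnerable than carriage, safety, interference with other vaccines and group 1 versus group 2, where expected differences are smaller. Group 2 versus group 3 is not affected.

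**What to change.** In viii) Data analysis, make the principal analysis of every contrast with group 1 stratified by or adjusted for block: a linear model for log IgG, Mantel-Haenszel or logistic regression for proportions, and Poisson regression with block for admissions. Only Blocks 2-4 then inform these contrasts. Add urban/rural as a stratification factor for precision. Keep Block 1 in group 2 versus group 3.

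In vii) Sample size requirements, state that group 1 contrasts rest on 104 versus 78 infants, with 83% of the pooled information. The planned 90% versus 70% contrast stays above 80% power. The carriage claim of 40% versus 22% does not, and must be restated for group 1 contrasts. The ALRI admission statement also covers group 1 and should be rechecked on the same basis.

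The change is to wording only and needs no extra infants or samples. The cost is a standard error about 9.5% larger for group 1 contrasts (1/sqrt(0.833) = 1.095).
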